### Qualitative data

Qualitative data transcribed verbatim from semi-structured interviews and focus groups will be analysed using a thematic analysis approach. A random sample of intervention audio recordings will be sampled to assess fidelity. High fidelity will be considered as  $\geq 80\%$  of intervention core components (as specified in the intervention manual) fully delivered by the therapist within each session.

Qualitative analysis will be completed by a member of the research team as data becomes available (completion of interviews/focus groups and/or availability of audio recordings to assess fidelity).

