## **6.2 Primary objectives**

The primary objective of this feasibility trial is to determine whether the intervention was delivered as intended considering the five domains of intervention fidelity (design, training, delivery, receipt, and enactment).

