|                                                                                                           | Walk continuously for 10-minutes outside with the use of two crutches with another person.                                                                       |

The programme will be supported by a maximum of six therapist home visits (target mean of four) to enable a treating therapist to provide supervised support for practice and progression of intermediate goals. Therapists will employ motivational interviewing (engage, focus, evoke and plan) during supervised sessions (see 9.5.5.5).

The participant will be asked to practice independently and/or with family/friends between therapist visits. They will be asked to document this practice in a diary (whether completed or not, independently or with another person, how felt during and after).

The goal-orientated mobility programme targets behaviour change techniques related to capability

(*commitment, behavioural contract*), opportunity (*action planning, habit formation*), and motivation (*goal setting*) for outdoor mobility at increasing distances from home.

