#### **• Home visit 1**

- a. Show video of older adults discussing their experiences of recovery. Provide piece of paper with link to video to watch again later.
- b. Outline intermediate goals in pursuit of the programme goal.
- c. Practice first intermediate goal while using MI strategies and BCTs (feedback and monitoring, framing/reframing, verbal persuasion about capability).
- d. Set plan for practice between home visits with social support as available (BCT – social support, restructuring the social environment, habit formation).
- e. Provide and describe how to complete home diary.
- f. Schedule next home visit.

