### 21.3 Figure 3: Progression criteria

|                                     | GO                                                              | AMEND                                                             | STOP                                                            |
|-------------------------------------|-----------------------------------------------------------------|-------------------------------------------------------------------|-----------------------------------------------------------------|
| Recruitment                  | ≥40% eligible                                                   | 21-39% eligible                                                   | ≤20% eligible                                                   |
| Recruitment                  | ≥50% eligible recruited                                         | 31-49% eligible recruited                                         | ≤30% eligible recruited                                         |
| Randomisation                | ≥70% of those recruited are randomised                          | 49-70% of those recruited are randomised                          | ≤48% of those recruited are randomised                          |
| Acceptability*, participants | Median of ≥28                                                   | Median of 24-27                                                   | Median of <24                                                   |
| Acceptability*, therapists   | Median of ≥28                                                   | Median of 24-27                                                   | Median of <24                                                   |
| Fidelity                     | ≥80% sessions included all intervention components as described | 51-79% sessions included all intervention components as described | ≤50% sessions included all intervention components as described |
| Outcome, 12-weeks            | ≥80% completeness of EQ5D at 12-week follow-up                  | 51-79% completeness of EQ5D at 12-week follow-up                  | ≤50% completeness of EQ5D at 12-week follow-up                  |
| Outcome, 6-months†           | ≥70% completeness of EQ5D at 6-month follow-up                  | 31-69% completeness of EQ5D at 6-month follow-up                  | ≤30% completeness of EQ5D at 6-month follow-up                  |

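### Fidelity, the primary objective, has two thresholds that do not agree: section 13.2 sets 80% of components within a session, Figure 3 sets 80% of sessions with every component

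*Protocol*

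**What the plan says.** Section 6.2 makes fidelity the primary objective: to "determine whether the intervention was delivered as intended considering the five domains of intervention fidelity".

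Section 13.2, under qualitative data, gives the measurement: "A random sample of intervention audio recordings will be sampled to assess fidelity". Fidelity is high when at least 80% "of intervention core components (as specified in the intervention manual) fully delivered by the therapist within each session". The 80% is a share of components inside a session. The section does not say how many sessions must reach it.

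Figure 3 (section 21.3), which section 15 names as the progression criteria, has a fidelity row with three bands:

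- GO: "≥80% sessions included all intervention components as described"
- AMEND: "51-79% sessions included all intervention components as described"
- STOP: "≤50% sessions included all intervention components as described"

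Here the percentage is a share of sessions, and a session counts only if nothing was left out.

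On the amount of delivery, section 9.5.5.2 allows a "maximum of six therapist home visits (target mean of four"). Section 9.5.5 lets the programme end once the goal is reached, after six visits, or at 12 weeks. No row of Figure 3 uses the number of visits delivered.

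**The concern.** The same figure, 80%, is attached to two different quantities, and the session-level standard differs: most components in one place, every component in the other. A session that omits one component of five meets the first standard and fails the second.

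The primary objective could therefore be reported as met by the definition in the analysis section while the progression table says STOP, or the reverse. Timing adds to this. Section 13.2 has qualitative analysis, including the recordings, done as material arrives, whereas the statistical analysis plan need only be final before database lock. The choice between the two standards could be made after fidelity results have been seen.

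A separate and smaller gap is that recordings and session scores exist only for sessions that happened. Section 6.1 asks whether the NHS can deliver the programme, yet neither threshold reflects how much of it was delivered.

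**Working it through.** The protocol gives no sample size or precision for fidelity, so there is no stated figure to reproduce on this point. Its one computed design figure, ±11% for retention, reproduces (48/60, exact 95% interval 67.7% to 89.2%, half-width 10.8 points) but has no bearing here.

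**Inputs from the protocol.** Section 13.2: at least 80% of components within a session. Figure 3: GO at 80% or more of sessions with all components, AMEND 51–79%, STOP at 50% or less. Section 13.1: 30 participants per arm. Section 9.5.5.2: target mean of four home visits. The number of core components per session is left to the intervention manual, which is not shown.

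**Case 1: every session delivers 4 of 5 components.**
- Section 13.2: 4/5 = 80% in each session, so every session is high fidelity.
- Figure 3: sessions with all components = 0%, so STOP.
- With 9 of 10 in every session the result is the same: 90% against 0%.

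**Case 2: 80% of sessions are complete and 20% deliver 3 of 10 components.**
- Figure 3: 80% of sessions complete, so GO.
- Section 13.2: the remaining sessions are at 30% and fail. If every session must reach 80%, fidelity is not high. If the label applies session by session, the section gives no overall verdict.
- Pooled over components the rate is 0.8 × 100% + 0.2 × 30% = 86%, a third possible summary.

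These two cases need no model and carry the point.

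**Illustration only.** Assume k components per session, each delivered independently with probability p. The share of complete sessions is p^k. The share reaching 80% of components is P(X ≥ 0.8k), with X binomial(k, p). For k = 5 and p = 0.90, the shares are 0.9^5 = 0.590 and 0.9^5 + 5 × 0.9^4 × 0.1 = 0.919.

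| k | Reach 80% of components (p = 0.90) | Complete (p = 0.90) | Figure 3 | p needed for GO, 0.8^(1/k) | p at which the expected share is 50%, 0.5^(1/k) |
|---|---|---|---|---|---|
| 5 | 92% | 59% | AMEND | 0.956 | 0.871 |
| 8 | 81% | 43% | STOP | 0.972 | 0.917 |
| 10 | 93% | 35% | STOP | 0.978 | 0.933 |

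The values of k and p are assumptions. The table shows only that the two standards can be far apart when delivery is good but imperfect.

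**Sessions that did not take place.** At the target mean, 30 × 4 = 120 home visits. Suppose the mean is 2, giving 30 × 2 = 60 visits, of which 90% (54) are complete. Figure 3 reads 54/60 = 90%, GO. Set against the 120 visits implied by the target, complete visits are 54/120 = 45%.

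**The case against.** Only Figure 3 carries GO, AMEND and STOP. Section 13.2 attaches a descriptive label, so the progression decision has a single written source. This stands, and it limits the claim: the conflict is between a definition of high fidelity and a gate, not between two gates. It does not remove the conflict, because both speak to the primary objective and can report opposite things.

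The kindest reading takes section 13.2 as the session-level standard and Figure 3 as the trial-level threshold. It fails because Figure 3 asks for all components, not 80% of them. Nor is this a detail left to the analysis plan: the protocol itself fixes both standards.

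Four stronger readings are tempting, and the protocol does not support them.

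- **Figure 3 cannot be met because content is visit-specific.** The first item of home visit 1 in section 9.5.7 is "Show video of older adults discussing their experiences of recovery", which need not recur. But Figure 3 says components as described, and that can be read as those due in the session. A clarification is needed; impossibility is not shown.
- **One visit counts as full fidelity.** Both rules score sessions, not participants, and a single visit passes only if its own components were delivered.
- **Missed sessions cause the conflict, or should be scored as failures.** They are a separate gap. The protocol sets no planned number of visits per participant and permits several early endings. Its treatment logs are completed after sessions that occurred, so nothing shows that reasons for missed sessions are recorded.
- **Modelled percentages predict this trial's result.** The lettered lines of the example schedule are not the manual's core components, and some are administrative.

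Missed delivery is also not invisible to the trial as a whole: barriers to delivery are a secondary objective, explored in interviews and focus groups.

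**Conclusion.** The point holds as a conflict of wording on the primary objective. Section 13.2 and Figure 3 use different session-level standards, and nothing reconciles them. In the clearest case the gap is total: every session is high fidelity under section 13.2 and 0% of sessions pass under Figure 3. The disagreement can also run the other way. This rests only on the two statements as printed and on a session being scored on five or ten components. The size of the gap in practice cannot be estimated without the manual's checklist.

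A reader might infer that the 80%-of-components standard is the intended one and the all-components wording a slip. The protocol does not show which was meant, and the choice matters, since the first is the easier to pass. The absence of any measure of visits delivered is a secondary reporting gap.

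**What to change.** Before any recording is scored, reconcile section 13.2 and Figure 3 into one rule and use it in both places. It should state:

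1. The session-level standard: either at least 80% or all of the components due in that session on the manual's checklist. The sponsor must choose and then keep it fixed.
2. The share of sessions needed for GO, AMEND and STOP.
3. Whether telephone sessions are in the denominator.

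Separately, report from the treatment logs the mean number of home visits delivered per intervention participant, including anyone who received none, against the target mean of four. Place it beside the fidelity result. Do not score permitted early endings (goal reached, six visits, 12 weeks) as failures.

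The cost is rewording in two places and slightly more reporting. The logs already named in section 7.1 supply the visit count. The downside is that the reported fidelity picture may look less favourable. If the sponsor chooses the 80%-of-components standard for Figure 3, that loosens the present gate and should be acknowledged as a change of criterion.

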## ***13.3 Interim analysis and data monitoring***

### **13.3.1 Discontinuation rules and breaking of randomisation code**

The TSDMC will monitor screening and recruitment rates and safety reporting; pooled data will be presented in open reports for review and discussion. Data by allocated group will be provided in separate, closed reports, for review and discussion by the TSDMC. There are no interim analyses planned.

The end of the study is the date when all data queries are resolved, and database locked which is anticipated to be month 17 from funding start. Should the research team/TSDMC deem a need for discontinuation of the trial (e.g., for urgent safety measures), the CI will report the early discontinuation via an NRES End of Study Declaration form to the main REC with a copy to the co-Sponsors.

There are no anticipated circumstances under which the randomisation codes may need to be broken.

### **13.3.2 Monitoring, quality control and assurance**

The trial will be conducted in compliance with the approved protocol, GCP, the UK General Data Protection Regulation and Data Protection Act (2018), the Trust Information Governance Policy (or other local equivalent), the UK Policy Framework for Health and Social Care Research, the Sponsor's Standard Operating Procedures, the Mental Capacity Act 2005, and other applicable regulations as required.

The trial will be led and managed by the CI with the support of the trial manager. This will include co-ordination of all day-to-day aspects of the trial from initial set-up to closeout, including: development of the systems, protocol and other essential documents; REC/HRA submission and amendments; set-up and management of trial management group (TMG) and TSDMC meetings; planning and provision of site initiation visit; day-to-day liaison with site; study monitoring oversight; safety management and reporting, progress reporting to REC, TSDMC, Sponsor and funder; performance of site closure at end of study; provision of end of study notifications to HRA and REC; preparation of files for archiving.

The CI will chair the TMG, which will also include the investigators, PPI representative, trial manager, and trial statisticians meeting at least bi-monthly throughout the trial and more frequently during the earlier phases. The TMG will closely monitor study progress, identifying and addressing practical, scientific, and financial issues as they arise. The TMG will report progress to the Sponsor and the independent TSDMC.

A joint TSDMC will be established prior to trial start to include the CI, trial manager, trial statistician(s), a sponsor representative, as well as the following independent members; Chair, statistician, PPI representative(s), clinician, and health services researcher. The Committee will provide advice, data monitoring (screening and recruitment rates), quality assurance, and safety monitoring (number, nature and outcomes for all SAEs). The Committee may include open and closed sessions. Closed

sessions will not be attended by the chief investigator or trial manager and may be used for data monitoring and/or other discussions at the discretion of the Chair. The Committee will be asked to recommend any necessary actions. It is anticipated that the Committee will meet every six months during the trial period.

A protocol deviation is defined as an unintended departure from the expected conduct of the study protocol, which does not need to be reported to the sponsor. The CI will monitor protocol deviations by monitoring treatment logs completed by treating therapists after each session against the treatment allocation. Any deviations noted will be listed in a deviation log. Significant deviations to the protocol or deviations which are found to frequently recur will be assessed by the CI to see if an amendment to the protocol is required. Any significant deviations to the protocol or recurring deviations will be reported to sponsor and action taken through Corrective and Preventative Actions.

A 'serious breach' is defined as a breach likely to effect to a significant degree:

- The safety or physical or mental integrity of the participants of the trial;
- The scientific value of the trial.

The CI and Sponsor will be notified by the site PI immediately via the study mailbox if a potential serious breach occurs. If the Sponsor determines the breach as serious, the breach will then be reported to the REC Committee with the sponsor in copy within 7 calendar days of the CI being notified.

The trial database will be programmed to generate notifications for possible data entry errors and missing key data points.

Prior to publication, the presentation of results (text, tables and figures) will be reviewed by the trial management group to ensure the anonymity of participants will be preserved. In particular, we will review variable level counts and identify any which are small and in combination with other data could render information potentially identifiable. If this occurs, we will categorize the variable further to ensure anonymity is preserved. If further categorization is not possible, we will suppress the potentially identifiable data and report the extent to which data suppression was employed in the results.

## **14 Public and patient involvement**

We involved patients and carers from proposal conception onwards. In 2020, [name] supported the establishment of a PPI group which meets quarterly to discuss Trauma Rehabilitation (Orthopaedic) research for Older People - 'TROOP'. TROOP includes men and women from different ethnic backgrounds who reside at home across England. We were awarded a NIHR Research Design Service Enabling Involvement Fund to support TROOP focus groups and participation in the intervention development workshop for the current project. Members of TROOP informed:

1. Potential outcome measures for a definitive trial (focus group 04/2021). We discussed the EQ-5D-5L, the Nottingham Extended Activities of Daily Living (NEADL) Scale and the University of Alabama Life Space Assessment as prospective primary outcome measures for a future definitive trial. All members were strongly in favour of the EQ-5D-5L as a more

global measure of quality of life. TROOP members suggested the NEADL and University of Alabama Life Space Assessment were valuable additions for understanding how the intervention may work.

2. Participant eligibility (focus group 07/2021). We discussed eligibility criteria for the feasibility trial. All members favoured adopting inclusive criteria which reflect the underlying population. Members proposed revising the lower age limit from 65-years to 60-years. Members agreed with proposed exclusion of those who resided in nursing home/residential care prefracture acknowledging that while these adults should be able to access rehabilitation, the make-up of an appropriate intervention would be different to that proposed here.
3. Intervention (workshops 08 & 09/2021). Members were given the opportunity to provide suggestions for the intervention and feedback on suggestions from others during two workshops. TROOP members suggested starting the intervention 30-days after hip fracture was appropriate and hearing the recovery experience of people who had hip fracture would be beneficial.
4. Review of lay summary and ongoing involvement plans (focus group 10/2021). Members reviewed the plain English summary for the proposal during a meeting and provided feedback over email after the meeting. For ongoing involvement, members suggested front-loading PPI with monthly meetings for first six months and quarterly TROOP meetings thereafter. A TROOP representative will join the trial management committee.

We will continue our active collaboration with PPI members of TROOP for the duration of the project. We will follow the UK Standards for Public Involvement to ensure this collaboration follows best practice and TROOP members continue to be reimbursed appropriately for all contributions.

[name] will take a leadership role for TROOP with respect to the current project and attend bimonthly trial management group meetings.

TROOP members will meet monthly on MS TEAMS for the first six months to ensure they are actively involved in protocol development, ethics, HRA and Local R&D approval processes. In particular, we will seek guidance from TROOP members on the participant information leaflet, consent forms, and proposed approaches for recruitment, data collection, and format of the intervention diary. During this initial six-months, TROOP members will also contribute to plans for the video of older adults who incurred hip fracture. They will support the formulation of interview questions, provide feedback on the proposed set up for the interviews, and provide feedback on the layout of the edited video.

TROOP members will then meet quarterly remotely for 90-minutes. These meetings will include discussion of progress, interpretation of qualitative and quantitative results, and development and dissemination of plain English summaries of the project findings.

TROOP members were offered a practice session to access MS TEAMS prior to attending their first TROOP meeting to ensure they were comfortable with how to join the meeting and that their camera and microphone were working. TROOP members are supported through circulation of materials by email or post -whichever is preferable. We also provided ergonomic pens and visual stress friendly notebooks for TROOP members (as required) to enable them to take notes during TROOP meetings. [name] will be sent materials (including an outline of the format) in advance of

each meeting. He will be offered a pre-meeting with the lead applicant to discuss anything that is not clear.

We have recruited two PPI members independent of TROOP for the TSDMC through NIHR People in Research.

## **15 Ethical considerations**

This trial is funded by the NIHR Research for Patient Benefit Scheme ([name] PI), the application for which underwent external peer review. The trial was designed in collaboration with PPI members of TROOP (see Section 14) and TROOP members will have an active role in the management of the trial, as well as in the interpretation and dissemination of the trial findings.

The study requires regulatory approval from the following bodies: NHS REC and HRA. Before any site can enrol patients into the study, the Chief Investigator/Principal Investigator or designee will ensure that the appropriate regulatory approvals have been issued, and NHS Confirmations of Capacity and Capability and Sponsor green lights are in place.

Participants will not be enrolled into the study until informed consent has been obtained, from adults with capacity to consent, by a suitably trained individual (clinicians or trust research staff). Older adults will require capacity to consent due to the safety profile of the intervention (the intervention includes unsupervised outdoor mobility). Non-English language speaking older adults will be supported to consider their enrolment in the trial with the use of local interpreting services.

Participants are free to withdraw from the trial at any point or a participant can be withdrawn by the CI/site PI. See Section 9.9 for further details. No sanctions will follow if the participant decides to leave the research at any time.

To mitigate the risk of ongoing uncertainty at the end of the feasibility trial, we propose progression criteria outlined in Figure 3.

The study will be monitored by the TMG and a TSDMC (See Section 13.3.2). All correspondence with the Sponsor, REC and HRA will be retained.

